#### Multivariate analysis

In order to analyse the efficacy of the intervention in improving balance from the baseline, considering each subject’s repeated measures (visits 2, 3 and 4) and the covariables of interest, we will use mixed linear models (using Generalised Estimation Equations, GEE) when treatment is a fixed factor, the CDP SOT percentage mean balance at baseline and over time post-intervention is a random effect and a Gaussian distribution function is considered.

All the data analyses will be performed using R software, version 2.9.1 [25].

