## Methods and design

### Aim of the study

The primary objective is to evaluate the effectiveness of a mobile posturographic system with vibrotactile neurofeedback to improve balance in elderly patients. Each subject was assessed immediately after the rehabilitation.

The secondary objectives are:To verify that improvements in balance are maintained in the medium term (six to twelve months).To consider whether this improvement in balance results in a reduction in the number of falls suffered by the elderly.To assess whether the reduction in the number of vestibular rehabilitation sessions (five) leads to similar results (an improvement in balance and a reduction in the number of falls) to those obtained after ten sessions. Both rehabilitation systems are compared using computerised dynamic posturography and mobile posturographic with vibrotactile neurofeedback.

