### Variables

The study variables shall be as follows:Date of birth.Sex.Weight (kg) and height (cm).Number of falls in the 12 months before inclusion.Hospitalisations due to falls over the previous 12 months.Percentage of mean balance (average) as observed in computerized dynamic posturography (CDP) sensory organisation test (SOT) (PRIMARY ENDPOINT); this will be obtained by calculating the mean of the scores of the 18 records of each sensory organisation test (calculated by software).DHI score: covered by patient.Short FES-I score: covered by patient.Duration (seconds) of TUG: measured by evaluator.Number of steps in TUG: measured by evaluator.Number of supports in TUG: measured by evaluator.Mean value of CDP SOT condition 5: calculated by software.Mean value of CDP SOT condition 6: calculated by software.CDP SOT vestibular contribution value: (mean value of condition 5/mean value of condition 1) × 100.Mean value of directional control of limits of stability in CDP: calculated by software.Mean endpoint value and maximum travel point of limits of stability in CDP: calculated by software.Vertiguard gSBDT value: calculated by software.Number of falls over 12 months after completion of VR programme (we will give the patient a timetable to allow them to check each fall immediately after it happens, in order to avoid memory bias).Hospitalisation resulting from those falls: date, diagnosis, duration of hospitalisation.

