### Analytical plan and statistical measures

The patients’ demographic data and characteristics will be described globally and by the covariables of interest, as will the patients’ results.

The continuous results will be summarised as mean, median, standard deviation (D) and interquartile range (P25, P75). For the categorical results, we will present the number and percentage of patients in each category.

The statistical analyses will be based on the complete analysis group (CAG), which comprises all the subjects (those who granted informed consent and met all the inclusion and exclusion criteria, and were randomised to one of the study arms).

**The outcomes** of interest are: balance assessment (average balance score in CDP SOT and Vertiguard’s gSBDT score, with possible values 0–100 in both); assessment of instability perception scales (DHI, short FES-I) on visits 2 (after intervention), 3 (6 months after intervention) and 4 (12 months after intervention); number of falls at 12 months post-intervention.

**The covariables of interest** are:Baseline patient characteristics: they include the variables specified for visit 0.Associated risk factors: age, sex, weight (kg), height (cm), previous falls (yes/no).Adherence to intervention (investigator’s direct observation).

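### The only adjusted efficacy model is wrongly specified (a mixed model fitted by GEE, with the response as the random effect) and names no term that would isolate the effect immediately after rehabilitation

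*Protocol article*

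**What the plan says.** All places are in the protocol article.

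- *Multivariate analysis*, model class and fixed part: "we will use mixed linear models (using Generalised Estimation Equations, GEE) when treatment is a fixed factor". No other fixed factor is named.
- *Multivariate analysis*, random part: "the CDP SOT percentage mean balance at baseline and over time post-intervention is a random effect". The patient is not named as the random unit.
- *Multivariate analysis*, repeated measures and covariates: "considering each subject’s repeated measures (visits 2, 3 and 4) and the covariables of interest". The covariables' place in the model is not given.
- *Analytical plan and statistical measures* lists the covariables. The first group is "Baseline patient characteristics: they include the variables specified for visit 0", and the visit 0 examination includes the CDP SOT. The others are age, sex, weight, height, previous falls and adherence. Neither visit nor treatment-by-visit is among them.
- *Variables* designates the CDP SOT mean balance percentage as the primary endpoint.
- *Aim of the study* follows the primary objective with "Each subject was assessed immediately after the rehabilitation". Maintenance at six to twelve months is a separate, secondary objective.
- *Bivariate analysis* gives changes from baseline to the end of intervention, 6 months and 12 months, with 95% CIs. Groups are compared by ANOVA or Kruskal-Wallis.

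**The concern.** The model sentence combines two incompatible methods and misassigns the parts of the model. A mixed model carries random effects. GEE is a marginal method that handles within-patient dependence through a working correlation and carries none. The sentence asks for both, then names the primary outcome as the random effect.

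Two things are at stake. First, analysts reading the sentence in good faith could fit materially different models, and the choice could be made after the data are seen. Second, without a treatment-by-visit term the treatment coefficient is an average over visits. It separates neither the immediate effect (primary objective) nor its durability (secondary objective). Where averaging pulls a contrast towards zero, it would also favour concluding that five sessions do as well as ten, which is another secondary objective.

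**Working it through.** **Step 1. The role of each element.**

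| Element | What the article says | Problem |
|---|---|---|
| Method | Mixed linear model, by GEE | GEE has no random effects |
| Random effect | SOT at baseline and over time | SOT is the response; the patient is not named |
| Baseline SOT | Outside the repeated measures (visits 2, 3, 4); inside the random-effect clause; a covariable through the visit 0 variables | Three roles that do not agree |
| Visit | Not named as a fixed term or listed as a covariable | No visit-specific mean |
| Treatment-by-visit | Not named | No visit-2 contrast |

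**Step 2. What the treatment coefficient estimates.** Take any two arms with complete, balanced data, an exchangeable correlation and no baseline difference. Without a treatment-by-visit term, the treatment coefficient is the simple mean of the between-arm differences over the occasions used as responses.

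- Reading A, baseline kept as a response, constant effect d: (0 + d + d + d)/4 = 0.75d, a 25% attenuation. For d = 5 this is 3.75.
- Reading B, baseline as a covariate and visits 2 to 4 as responses, constant effect d: (d + d + d)/3 = d, no distortion.
- Assumed fade of 5, 3 and 1 points at visits 2, 3 and 4: (5 + 3 + 1)/3 = 3.0 under Reading B and (0 + 5 + 3 + 1)/4 = 2.25 under Reading A, against 5 at visit 2.

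**Step 3. Check by simulation.** Two arms of 55 (the planned arm size), four occasions, exchangeable GEE, 300 replicates, true visit-2 effect of 10 points. The visit means of 64, 73 and 74 come from *Calculation of sample size*. The 6-month mean of 73.5, an SD of 15 and a within-patient correlation of 0.6 are assumptions, because the article gives none of them.

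| Analysis | Constant 10/10/10 | Assumed fade 10/5/0 |
|---|---|---|
| Baseline as response, treatment only | 7.4 | 3.9 |
| Baseline as covariate, no treatment-by-visit | 10.0 | 5.1 |
| Baseline as covariate, visit and treatment-by-visit: visit-2 contrast | 10.0 | 10.1 |
| Difference in change from baseline at visit 2 (the ANOVA comparison) | 10.0 | 10.1 |

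The arithmetic of Step 2 predicts 7.5 and 3.75 for the first row, and 10 and 5 for the second. The simulation agrees within its noise. The last two rows recover the visit-2 effect under both patterns.

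The plan states no figure for this model that could be reproduced.

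**The case against.** A reader might infer that the trial has no valid estimate at its primary time point, or that its primary estimate will be diluted by 25%. The documents support neither.

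- *Bivariate analysis* already compares groups on change from baseline to the end of intervention. That is a visit-2 comparison, and Step 3 shows that it recovers the effect. It is unadjusted, but it exists.
- Neither analysis is labelled primary, so the adjusted model cannot be assumed to supply the primary estimate.
- Baseline SOT is available as a covariable, so it is too strong to say that nothing besides treatment enters the model.
- The 0.75d figure needs baseline to be a response, yet the same sentence lists the repeated measures as visits 2, 3 and 4.
- No fade is documented. The only time course, in *Calculation of sample size*, is 73 after rehabilitation and 74 at 12 months. It is a within-group course, so it does not show that a between-arm difference stays constant, but it gives no support to any particular fade.
- The random-effect clause may have been meant as a patient-level random intercept (baseline) and slope (over time).

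All of these limit the reach of the point. They do not repair the sentence. The benign reading still conflicts with GEE, is not what is written, and supplies no treatment-by-visit term.

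It can also be said that covariance structure, further interactions and missing-data handling belong in a full analysis plan that is not shown. That is fair, and they are not raised as defects here. In particular, the stronger missing-data assumption of unweighted GEE is no finding, since the article gives no dropout pattern. The point is what the article states wrongly.

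**Conclusion.** The point holds as a specification error in the only adjusted efficacy model. The model class and the random effect contradict each other, the response is given the patient's place, and baseline SOT has three incompatible roles. No term isolates the effect immediately after rehabilitation.

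The numerical consequence depends on the reading: a 25% attenuation if baseline is a response and the effect is constant, none if baseline is a covariate and the effect is constant, and an average such as 3.0 against 5 if the effect is assumed to fade. These figures assume balanced, complete data with no baseline difference, and the fade is illustrative only. That the model cannot be fitted as written, and gives at best a visit-averaged effect, depends on none of these numbers.

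The criticism applies to this model and not to the whole plan. The remaining gap at plan level is that the article does not say whether this model or the unadjusted comparison of change is primary.

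**What to change.** Rewrite the model sentence in *Multivariate analysis* as follows.

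1. Response: CDP SOT mean balance at visits 2, 3 and 4.
2. Fixed terms: baseline SOT as a covariate, treatment arm, visit (categorical) and treatment-by-visit.
3. Within-patient correlation: either a linear mixed model with the patient as the random unit (or a patient-level covariance structure), or GEE with a stated working correlation. Choose one, not both. Either is acceptable with this mean model.
4. Primary estimate: the visit-2 treatment contrast with its 95% CI. The visit 3 and 4 contrasts answer the durability objective.
5. State that the *Bivariate analysis* comparison of change is supportive, so that only one analysis is primary.

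The cost is wording in the protocol or analysis plan. No additional data, visits or patients are needed, and either model is standard in R. The change should be made before the outcome data are analysed.

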#### Bivariate analysis

We will provide the differences (95% CI) in the balance test assessments between baseline and end of intervention, and 6 months and 12 months post-intervention. These measures will be compared between groups by ANOVA or the Kruskall-Wallis test if normality is not assumed.

The Chi-squared test or Fisher’s exact test, depending on the conditions, will be used to analyse the number of falls occurring from 12 months prior to inclusion and 12 months post-intervention.

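### The only between-arm analysis spelled out for gSBDT is an unadjusted change-score test, which gives up precision that its visit 0 value could supply

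*Protocol article*

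**What the plan says.** All places are in the protocol article.

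- *Analytical plan and statistical measures* defines the balance assessment by two scores: "average balance score in CDP SOT and Vertiguard’s gSBDT score, with possible values 0–100 in both". It also lists the covariables, among them: "Baseline patient characteristics: they include the variables specified for visit 0". The section on pre-screening visit 0 places the gSBDT at that visit.
- *Variables* marks SOT as the primary endpoint, so gSBDT is secondary.
- *Bivariate analysis* promises the "differences (95% CI) in the balance test assessments between baseline and end of intervention, and 6 months and 12 months post-intervention". It then states: "These measures will be compared between groups by ANOVA or the Kruskall-Wallis test if normality is not assumed". No baseline covariate enters this comparison.
- *Multivariate analysis* opens with a general purpose: "In order to analyse the efficacy of the intervention in improving balance from the baseline". It uses the repeated measures of visits 2, 3 and 4 and the listed covariables. When it specifies the model, the only measure it names is SOT: "the CDP SOT percentage mean balance at baseline and over time post-intervention is a random effect".

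**The concern.** Both balance scores have a baseline and three follow-up values, but only SOT is named in a model that takes covariates. For gSBDT, the comparison actually written down is a test of raw changes.

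A change score subtracts the whole baseline value, while the best prediction of the follow-up value usually uses only part of it. The excess adds noise to every between-arm contrast. If one arm starts worse on gSBDT by chance, that arm will also tend to show the larger gain.

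Two features of this trial give the loss some weight. Arms A and B train on the platform that produces SOT, and arms C and D train on the device that produces gSBDT, so each score is measured on one side's training equipment. A secondary objective also asks whether five sessions give results similar to ten, and wider intervals make a statement of similarity harder to support.

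**Working it through.** **The plan's own figure.** *Calculation of sample size* gives 53 per arm, 4 × 53 = 212, raised to 4 × 55 = 220. It concerns SOT and states no standard deviation, so it can be neither reproduced nor refuted. For a two-sided two-sample test at 5% with 80% power, it would need an SD of 18.4 for a 10-point difference, or 16.5 for 9 points. Nothing below depends on it; only the total of 220 is used.

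**Inputs.** N = 220 (from the article). The baseline-to-follow-up correlation ρ of gSBDT is not given, so it is an assumption, shown over a range. The formulas take one follow-up visit, a common variance s² at baseline and follow-up, and all 220 patients contributing.

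**Formulas.** The per-patient variance that drives any contrast between arms is:

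- change score: 2(1 − ρ)s²
- follow-up adjusted for baseline: (1 − ρ²)s²

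The efficiency of the change score relative to adjustment is (1 − ρ²) / [2(1 − ρ)] = (1 + ρ)/2. The equivalent N is 220(1 + ρ)/2. The interval is wider by a factor of √[2/(1 + ρ)].

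| ρ (assumed) | Variance ratio 2/(1 + ρ) | Equivalent N of 220 | Interval wider by |
|---|---|---|---|
| 0.3 | 1.54 | 143 | 24% |
| 0.5 | 1.33 | 165 | 15% |
| 0.7 | 1.18 | 187 | 8% |
| 0.8 | 1.11 | 198 | 5% |

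At ρ = 0.5: 220 × 1.5/2 = 165. With 212 patients it would be 212 × 0.75 = 159. A simulation of four arms of 55 at ρ = 0.5 (6,000 runs) gave an efficiency of 0.754 against the theoretical 0.75. The ratio refers to the ANOVA on changes and was not worked out for the Kruskal-Wallis alternative.

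**Chance imbalance.** With 55 per arm, the standard error of a baseline difference between two arms is √(2/55) = 0.19 SD. At ρ = 0.5, an imbalance of that size shifts the change-score contrast by (1 − 0.5) × 0.19, about 0.1 SD, in favour of the arm that started worse.

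**If entry criteria narrow the baseline variance.** Assume a slope of 0.5, a residual variance of 0.75 and a baseline variance halved from 1 to 0.5.

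- Var(change) = (1 − 0.5)² × 0.5 + 0.75 = 0.875
- Var(adjusted) = 0.75
- Ratio = 0.875/0.75 = 1.17, and 220/1.17 is about 189

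The within-sample correlation in that case is about 0.38. The equal-variance formula at 0.38 would give about 152, so it overstates the loss when selection has narrowed the baseline.

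**The case against.** The strongest reply is that gSBDT may already be inside the model. The stated purpose of the multivariate step is balance in general, balance is defined by both scores, and the covariables include those of visit 0. A bivariate step followed by a multivariate one is the usual unadjusted-then-adjusted sequence, and naming the primary endpoint does not rule out applying the model to the second score. This stands as a possible intention. It does not settle the matter, because no sentence names gSBDT as a response or its own baseline as the covariate for it.

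A reader might infer more than the article supports:

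- *That the non-SOT baselines go unused.* The covariable list includes the visit 0 variables, and the model refers to that list.
- *That the gSBDT comparison is biased.* Averaged over randomisations, a change-score contrast is unbiased. Regression to the mean from the entry criteria acts on all arms alike, and a distortion needs a chance imbalance. The gSBDT criterion is also only one of five, any two of which suffice.
- *That DHI and Short FES-I are wrongly left without an analysis.* They are listed as outcomes, "assessment of instability perception scales (DHI, short FES-I) on visits 2 (after intervention), 3 (6 months after intervention) and 4", with no method named for them. *Data collection and ethics* counts the questionnaires among the tests of the balance study, so the bivariate step may cover them. If it does not, a condensed article may leave this to the full plan.
- *That gSBDT serves as a check on the SOT result.* Nothing in the article says so.

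It also stands that no power is claimed for gSBDT and that no value of ρ is documented.

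**Conclusion.** The point holds as a limited one about a secondary outcome. As written, the only between-arm analysis spelled out for gSBDT is an unadjusted change-score test, and a more precise analysis is available from data already collected.

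Under equal variances at a single visit, the loss corresponds to analysing about 143 to 198 of 220 patients for ρ from 0.3 to 0.8. It is positive for every ρ below 1, fades as ρ rises, and is smaller if selection has narrowed the baseline spread. No single figure in that range can be called the trial's own. The cost is in precision; the validity of the comparison is touched only conditionally, when the arms differ at baseline by chance.

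**What to change.** In *Multivariate analysis*, name gSBDT as a response alongside SOT, with its own visit 0 value entered as a fixed covariate. The wording should say fixed, because the present sentence places the baseline under a random effect. Take the between-arm differences with 95% CIs at visits 2, 3 and 4 from that model. In *Bivariate analysis*, label the change-score comparison as descriptive or supportive.

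The same model can be used for DHI and Short FES-I, each with its own visit 0 value, as an optional extension.

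The cost is a few lines of analysis-plan text. The baselines are already collected, and no further patients, visits or measurements are needed.

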## Discussion

Reducing the number of falls among aged patients (and thus the related injuries and cost) is a goal that can be directly related to the ongoing 2020 European social programme (Healthcare, demographic change and well-being). One of the goals of this programme is to help aged patients stay active and healthy, by promoting active ageing, and a healthy and autonomous lifestyle, as well by helping aged patients to look after their own health. Aged population groups are especially exposed to cognitive impairment and are at risk of social exclusion. This has negative consequences on their independence and their quality of life, the independence of those who care for them and the sustainability of public healthcare systems. Europe faces a dwindling and ageing population. In 2050, the number of citizens aged over 65 will increase by 70%, and the number of those over 80 will grow by 170%.

Vestibular rehabilitation (and especially computerized dynamic posturography training) has been proven to be useful for improving balance and reducing the number of falls among the aged. However, the elevated cost of dynamic posturography has limited its use; the number of sessions currently prescribed (the average is approximately 10), limits the number of patients who can use this technique.

In order to increase efficiency and improve the cost-benefit function of vestibular rehabilitation as a mechanism to reduce the number of falls among aged patients, it is important to select particularly vulnerable groups. These groups can be established on the basis of several criteria, such as balance metrics [26, 27], age [28] and morphotypes [29]. We must prioritise these vulnerable groups.

It is also possible to implement two strategies that improve the cost-benefit of posturography. The first involves optimising the number of rehabilitation sessions. Although this number must be adjusted to the specific needs of each patient, the average is approximately 10. However, in certain patients who suffer from instability due to unilateral vestibular balance deficits, regardless of age, it has been proven that groups of five and of ten session programmes both have similar effects [16]. These data are, obviously, not directly extrapolate to elderly patients with instability, because in cases due to unilateral vestibular dysfunction, the deficit lies in only one labyrinth, and the deficit can be compensated with the remaining relevant sensorial systems (the other labyrinth, sight and the proprioceptive system) more easily. Age-related balance deficits, however, generally have multiple causes, and are a result of poorly managed sensory information. In any case, we think it is worth exploring this possibility because, if the results of five and ten rehabilitation session are similar, it would be possible to reduce the cost of vestibular rehabilitation by half, which would also increase the chances of patients undertaking all the rehabilitation treatment.

The second cost-reducing strategy is based on the use of cheaper posturography systems. One alternative to computerised dynamic posturography is the mobile posturography device Vertiguard® (Vesticure GmbH, Germany), which analyses the motions of the centre of gravity over the course of different daily activities, both static (standing with eyes open and closed in different postures) and walking (open and closed eyes, head in motion, navigating around obstacles) [17]. The device, which is placed on a belt on the patient’s waist, has four vibrators (front, back, left and right). These vibrators produce a vibrotactile stimulus which helps the patient maintain a stable centre of gravity over the course of different exercises, and thus the analysis can be undertaken while the patient is carrying out vestibular rehabilitation exercises. This device is considerably cheaper than dynamic posturography systems, and is of small size, which allows for ambulatory posturography vestibular rehabilitation. The efficiency of this technique has been demonstrated for the treatment of different pathologies [18, 19]. However, to date no extensive and systematic studies have been undertaken that compare it with dynamic posturography in the treatment of age-related balance deficits.

The main limitations of the study are the next:Despite being an open study, we do not believe that the VR and assessment tests being performed by the same person introduces substantial bias since the results are provided by software and not interpreted by an individual.When asking about the number of falls in the 12 months before inclusion, there could be memory bias. We will try to modulate this by requesting confirmation from a family member who lives with the patient. We will also check the information about falls over that period against the information contained in the patient’s electronic medical records (IANUS).

